### 2.7. Statistical Analysis

Statistical analyses will be performed using SPSS version. 24.0 [73]. Descriptive analyses will be conducted on the experimental group and control group. After preliminary statistical assumption satisfaction, an independent samples T-test will be used to determine whether the groups differ in the psychodiagnostic measures administered at baseline. These potential differences will be used as covariates in the model. A multivariate analysis of covariance (MANCOVA) will then be conducted (factors: experimental group, control group, time; dependent variables: scores obtained in the neuropsychological and psychological measures; covariates: scores obtained in the psychodiagnostic measures at baseline). We will adopt this design because the dependent variables concerning the executive functions (WCST, alternate fluency, and TMT), as well as visuo-perceptive processing (ROCF-C), are moderately but significantly associated, given their involvement in frontal lobe abilities.

Partial eta-squared will be used to determine the effect size of the intervention. The analysis will be performed by an independent statistician, blinded to the treatment allocation, who will discuss the results with the researchers. Missing data will be handled using appropriate statistical methods to minimize bias and ensure robust results.

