Therefore, the present multicenter randomized controlled trial (RCT) aims to implement and evaluate a personalized CA-CRT program for individuals with AN as an adjunct to standard nutritional rehabilitation (treatment as usual, TAU). The study will test the feasibility and efficacy of CA-CRT in enhancing selected neuropsychological outcomes (cognitive flexibility and central coherence) and psychological measures (eating disorder symptomatology, health-related quality of life, and motivation to change) among inpatients with AN. The feasibility of the study will be evaluated through indices such as the recruitment and retention rates and the patient outcomes. These metrics will help determine not only whether the intervention is acceptable but also whether it can be implemented in routine clinical settings. By delivering a structured, scalable, and individually tailored intervention, the trial seeks to promote more effective, patient-centered care approaches. It is hypothesized that participants allocated to the experimental group will demonstrate greater improvements in the targeted outcomes compared to those receiving standard care alone over the 5-week intervention period. Specifically, the primary hypothesis is that participants in the CA-CRT group will show significantly greater improvement from baseline to post-treatment than those in the TAU group in relation to cognitive flexibility, as measured by the Wisconsin Card Sorting Test (WCST), the Phonemic/Semantic Alternate Fluency Test, the Trail Making Test (TMT), the Test of Attentional Performance (TAP), the Detail and Flexibility Questionnaire (DFlex), and the Cognitive Flexibility Inventory (CFI). Improvements are also expected in the Central Coherence Index (CCI) of the Rey–Osterrieth Complex Figure (ROCF-C).

The secondary hypothesis is that the CA-CRT group will show greater reductions in their eating disorder symptoms (EDE-Q), as well as greater improvements in their quality of life (WHOQOL-BREF) and readiness to change (URICA), compared to those receiving TAU.

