Moreover, the Standard Progressive Matrices (SPM) [54,55] will be administered. It consists of 60 items measuring nonverbal intelligence divided into 5 sheets (12 items each). Each item requires completion of a series of figures with a missing part that is presented among distractors, according to an increasing difficulty criterion.

Then, the Italian versions of the following neuropsychological tests will be collected pre- and post-treatment and used as the primary outcomes.

The Wisconsin Card Sorting Test (WCST) [56,57] will be used to assess abstract reasoning, mental flexibility, and problem-solving. The examinee has to match stimulus cards to one of four category cards. Cards can be matched by shape (cross, circle, triangle, star), color (red, blue, yellow, green), and number (one, two, three, four). The rule must be worked out by the feedback provided by the examiner (“right” or “wrong” response). When a rule is identified (i.e., 10 consecutive correct matches), the examiner changes the criterion without saying anything, and the examinee has to identify the new rule. Scoring provides the following indices: total mistakes, total correct responses, completed categories, perseverative mistakes, non-perseverative mistakes, percentages of perseverative mistakes, attempts to complete the first category, inability to retain the criterion, and task learning.

The Phonemic/Semantic Alternate Fluency Test [58] will be used to assess the verbal set-shifting ability. The examinee has to produce word pairs unusually, starting from a phonemic cue (letter A, F, S) and a semantic cue (color, animal, fruit), in 60 s. The raw score (number of word pairs obtained for each association (A–color; F–animal; S–fruit)) is adjusted for age, education, and gender; thus, it is converted into an equivalent score. Moreover, a composite shift index evaluating working memory is determined as follows: Total Alternate Fluencies/(Total Phonemic Fluencies + Total Semantic Fluencies/2).

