### 2.6. Procedure

Patients with AN will be invited to take part in the study at admission to the rehabilitation centers, according to the above-mentioned inclusion/exclusion criteria.

Before the randomization, they will be asked to sign the informed consent to participate in the study and to complete the psychodiagnostic (BAI, BDI II, OCI-R) measures.

Randomization will then be stratified by center and performed using the permuted block technique within each site by a researcher independent of the study. Participants will be assigned to one of two conditions: both groups will receive the usual hospital care (TAU), and the experimental group, in addition, will receive the CA-CRT treatment.

Before starting the program, all the participants will undergo neuropsychological testing (primary measures) and complete self-report psychological questionnaires (secondary measures).

The standard nutritional rehabilitation program is set up as a multidisciplinary treatment approach merging group therapies, individual therapies, and dietetic management in line with national guidelines [45]. Dietetic rehabilitation aims to encourage a change in eating habits and includes mealtime supervision, as well as both individual and group counseling provided by dietitians.

Individual sessions last from 30 to 45 min and encompass dietary assessment, evaluation of nutrient intake and adequacy, nutritional and anthropometric status, eating patterns, weight history, and patients’ readiness to change. Group meetings of around 20 people are provided every week and last about one hour. The main topics discussed include biological hunger, satiety, nutrients, weight management, and behavior change strategies for preventing relapse.

The patients’ meal plan is determined by the dietitian to gain half a kilogram (one pound) per week.

Meals last 60 min, followed by a 30 min mandatory resting period, where patients and staff members are together in a dedicated room. There are staff members present at all times during the meal and resting period.

Psychotherapy is provided once a week by a licensed psychotherapist in an individual setting and lasts about 45 min. Further, 1 h psychoeducational groups led by educationalists, psychologists–psychotherapists, or psychiatrists and focused on the relationship between food and emotions are provided weekly.

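### Covariates depend on baseline t-tests between randomized arms, which conflicts with the covariate list that follows, and neither the outcome's own baseline score nor centre is a covariate

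*Protocol article*

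**What the plan says.** Section 2.7 sets out the analysis in three steps.

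- Baseline comparison: "an independent samples T-test will be used to determine whether the groups differ in the psychodiagnostic measures administered at baseline".
- Consequence: "These potential differences will be used as covariates in the model".
- Model: a MANCOVA with "factors: experimental group, control group, time", "dependent variables: scores obtained in the neuropsychological and psychological measures" and "covariates: scores obtained in the psychodiagnostic measures at baseline".

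Section 2.6 identifies the psychodiagnostic measures. Before randomization, patients "complete the psychodiagnostic (BAI, BDI II, OCI-R) measures". Section 2.5 says that the "neuropsychological tests will be collected pre- and post-treatment and used as the primary outcomes". The primary hypothesis in the Introduction is "significantly greater improvement from baseline to post-treatment than those in the TAU group in relation to cognitive flexibility". Section 2.3 sizes the trial on an interaction effect. Sections 2.4 and 2.6 stratify randomization by centre, but centre is among neither the factors nor the covariates in Section 2.7.

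**The concern.** The psychodiagnostic scores are obtained before allocation, so any difference between the arms is due to chance. A significance test of that difference answers no useful question, yet here it decides which covariates enter. A covariate earns its place by predicting the outcome, not by being out of balance.

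The model sentence then names the same scores without the condition. Two statisticians following Section 2.7 could therefore fit different primary models, one with a fixed set and one with whatever the t-tests flagged.

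The baseline value of the outcome itself, usually its strongest predictor, is used only as the first level of time. Precision that could be had from data already collected is given up.

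**Working it through.** **1. The plan's own figure.** Inputs from Section 2.3: Pillai V = 0.2, effect size 0.5, α = 0.05, power 0.95, 54 participants per centre. For a group-by-time interaction with two groups and two time points:

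- f² = V/(1 − V) = 0.2/0.8 = 0.25, so f = 0.5.
- Noncentrality = N·f² = 54 × 0.25 = 13.5, on F(1, 52).
- Power is 0.9501 at N = 54 and 0.9464 at N = 53.

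The stated 54 is reproduced. With two time points this is a test of the difference in mean change, and f = 0.5 corresponds to a standardized difference in change of 2f = 1.0.

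**2. Chance selection.** Assume three totals, each tested at 0.05 (Section 2.7 gives no level). If they are independent, P(at least one enters) = 1 − 0.95³ = 14.3%. In simulation with an assumed mutual correlation of 0.5 it was about 13%.

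**3. Type I error.** One outcome was simulated, with 20,000 trials per scenario (Monte Carlo standard error √(0.05 × 0.95/20,000) ≈ 0.0015), three candidate covariates and an assumed pre-post correlation of 0.6.

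| Per arm | Covariate correlation with pre / post score | Change test, t-test-selected covariates | Change test, fixed covariates |
|---|---|---|---|
| 27 | 0.3 / 0.3 | 0.0495 | 0.0483 |
| 27 | 0.5 / 0.5 | 0.0486 | 0.0498 |
| 27 | 0.1 / 0.5 | 0.0389 | 0.0497 |
| 81 | 0.1 / 0.5 | 0.0390 | 0.0518 |

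Selection does nothing when the covariates relate equally to both visits. It is mildly conservative when they relate mainly to the post-treatment score.

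**4. Precision.** With equal variance σ² at both visits and correlation ρ, a change score has variance 2σ²(1 − ρ), and the post score adjusted for baseline has σ²(1 − ρ²). The ratio is 2/(1 + ρ). Scaling f² = 0.25 by this ratio, with one further degree of freedom spent, gives the following. The protocol gives no ρ, so a range is shown.

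| ρ | Change variance / ANCOVA variance | ANCOVA N for 95% power | ANCOVA power at N = 54 |
|---|---|---|---|
| 0.3 | 1.54 | 36 | 99.4% |
| 0.5 | 1.33 | 42 | 98.6% |
| 0.6 | 1.25 | 44 | 98.1% |
| 0.7 | 1.18 | 47 | 97.4% |
| 0.8 | 1.11 | 49 | 96.7% |
| 0.9 | 1.05 | 52 | 95.9% |

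A simulation at ρ = 0.6 with 27 per arm (8,000 trials, covariates correlated 0.3 with both visits) agrees: power was 0.950 for the change test with selected covariates, 0.980 for ANCOVA on own baseline, and 0.977 when the three totals were added.

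**5. A smaller effect.** At ρ = 0.6 the planning effect equals √(2 × 0.4) = 0.89 SD of the post score. With an assumed effect of 0.4 SD and N = 3 × 54 = 162, simulated power (4,000 trials) was about 80% for the planned approach and 87-88% for ANCOVA with own baseline, covariate and centre, when covariate and centre effects are the same at both visits.

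**The case against.** The strongest defence is that the planned test is sound. Time is a factor, outcomes are measured twice, the hypothesis concerns improvement and the sample size is built on the interaction. Baseline is therefore used, through change, and the comparison is valid under randomization. This stands. A reader might infer that baseline outcome scores are ignored; the documents do not support that. What remains is a loss of efficiency.

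A reader might also infer that covariate selection inflates the false-positive rate. The simulations show about 0.04 to 0.05 and never inflation.

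Two larger figures are tempting and should not be used.

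- Counting two BDI-II and six OCI-R subscales plus three totals gives 1 − 0.95¹¹ = 43% for chance selection. Section 2.7 does not say that subscales are tested, and totals overlap with their subscales, so the independence formula does not apply.
- Under the 0.4 SD effect in the working, a power gap of about 74% against 88% appears only if covariate and centre effects act on the post score alone. Even then, fixing the covariates moves power only from about 73% to 78%; baseline and centre adjustment supply the rest. With effects equal at both visits, selected and fixed psychodiagnostic covariates gave 80.2% and 80.3%.

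Finally, a condensed article may leave the exact covariate set to an analysis plan. That would excuse silence, but Section 2.7 is not silent: it states a selection rule and then a list that disagrees with it.

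**Conclusion.** The point holds as a conflict in the text and a free improvement, not as a threat to validity. Section 2.7 makes the covariates depend on tests between randomized arms and then lists them unconditionally. Chance entry of at least one of three totals is about 13-14%, and the consequence for type I error is nil to mildly conservative.

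The change-score comparison is valid but carries 5% to 54% more variance than ANCOVA for ρ from 0.9 to 0.3. At the protocol's large planning effect the gain is modest, from 95% to about 98% power at N = 54 and ρ = 0.6. It is larger at smaller effects, about 7 to 8 percentage points in the 0.4 SD example. Leaving out centre, the stratification factor, adds to the case for revising the model.

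The correlations, the 0.4 SD effect and the covariate strengths are assumptions. The calculations treat one outcome at a time, not the full multivariate test.

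**What to change.** Delete the baseline t-test and the sentence that turns its result into covariates, and present baseline data descriptively. Fix the covariates in advance: the baseline value of the outcome being analysed, the BAI, BDI-II and OCI-R totals, and centre. Model the post-treatment score by ANCOVA.

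One further matter has to be settled. Section 2.6 describes baseline outcome testing after the randomization step, while Section 2.4 dates assignment from the baseline assessment, which implies the reverse order. Reconcile the two so that baseline outcomes are measured before allocation. Participants know their arm, so a baseline taken afterwards could be affected by it. A constrained-baseline mixed model, the usual alternative to ANCOVA, requires a baseline measured before allocation.

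The analysis change is wording only, needs no new data, and should be made before any comparative data are seen. The timing point may need a change in procedure if testing is in fact done after allocation.

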Each subtest is preceded by a run-in, and the difficulty level of the task may change, according to the examiner’s guide. The TAP subtests are measured by the reaction times and accuracy determined as correct responses, false responses, omissions, and anticipations (i.e., responses within 100 ms).

The Detail and Flexibility Questionnaire (DFlex) [64,65]: A self-report questionnaire consisting of 24 items on a 6-point Likert scale (from 1 = strongly disagree to 6 = strongly agree) and assessing cognitive rigidity (RC, 12 items) and attention to detail (AD, 12 items). The subscale scores range from 12 to 72 and are calculated by summing the RC items and the AD items.

The Cognitive Flexibility Inventory (CFI) [66,67]: A self-report questionnaire consisting of 20 items used to assess two different subscales: the Alternative subscale, which evaluates the ability to perceive multiple alternative explanations for life events and human behavior, and the ability to generate multiple alternative solutions to difficult situations; and the Control subscale, which assesses the tendency to perceive difficult situations as controllable. Each item is scored on a 7-point Likert scale (from 1 = strongly disagree to 7 = strongly agree). The scoring requires inverse scoring of the selected items. The total score is calculated by the sum of all the items. Higher scores indicate greater cognitive adaptability and flexibility to be used in stressful situations; lower scores indicate greater cognitive rigidity associated with less cognitive flexibility in stressful situations.

The Italian versions of the following psychological measures will be also collected pre/post-treatment and used as secondary outcomes.

The Eating Disorder Examination Questionnaire (EDE-Q) [68,69] is a self-report questionnaire consisting of 33 mixed-type items (yes/no, 7-point Likert scales and visual analog scales) assessing the core symptoms of the eating disorder in the past 28 days. The EDE-Q has four subscales (i.e., Restraint, Eating Concern, Shape Concern, and Weight Concern) and a global score is calculated by the mean of all four subscales. Higher scores indicate an elevated frequency or clinical severity of eating disorder symptoms.

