## 3. Expected Results

To our knowledge, this will be the first RCT aimed at evaluating the feasibility and efficacy of CA-CRT in inpatients with AN undergoing nutritional rehabilitation. By delivering an individualized, structured intervention targeting specific cognitive deficits, this study aims to address the inconsistent conclusions highlighted in prior meta-analytic work [23]. It is expected that participants in the experimental group will demonstrate greater improvements in the neuropsychological outcomes—including cognitive flexibility, verbal fluency, visuospatial processing, and attention—as well as the psychological measures such as eating disorder symptomatology, health-related quality of life, and motivation to change. Participants are anticipated to develop a more flexible and integrative thinking style tailored to their unique cognitive profiles. Additionally, conducting the study across multiple specialized centers will enhance the generalizability and external validity of the findings, supporting the broader implementation of personalized, scalable therapeutic approaches for AN.

Still, several potential limitations should be considered in terms of the present study design. First, although the randomized controlled design strengthens the internal validity, recruitment will be conducted in a limited number of specialized clinical centers, which may reduce the generalizability of the findings to other settings or the broader population of individuals with AN. Second, the study will rely on a pre–post assessment with no intermediate follow-up; as a result, it will not be possible to evaluate the persistence of the treatment effects over time. Third, the inclusion of multiple neuropsychological and psychological measures increases the comprehensiveness of the assessment but also raises the potential for type I errors. Fourth, the intervention will be delivered in addition to standard rehabilitation treatment, which could vary between participants and centers, introducing heterogeneity that may influence the outcomes. Last, for ethical reasons, it will not be possible to control for participants’ pharmacological treatment or to restrict access to other forms of psychotherapy before or during the trial; while these factors will be recorded, they may introduce variability in the treatment response.

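### The single MANCOVA takes primary and secondary measures as joint dependent variables, so a significant result would not establish an effect on cognitive flexibility

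*Protocol article*

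**What the plan says.** The Introduction sets two hypotheses apart. The primary one reads: "participants in the CA-CRT group will show significantly greater improvement from baseline to post-treatment than those in the TAU group in relation to cognitive flexibility". The instruments named for it are WCST, alternate fluency, TMT, TAP, DFlex and CFI. A further sentence expects improvement in the Central Coherence Index of the ROCF-C. The secondary hypothesis covers EDE-Q, WHOQOL-BREF and URICA.

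Section 2.5 (Measures) keeps the division. For the first set: "neuropsychological tests will be collected pre- and post-treatment and used as the primary outcomes". For the second: "psychological measures will be also collected pre/post-treatment and used as secondary outcomes". Section 2.6 (Procedure) again uses the labels primary and secondary.

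Section 2.7 (Statistical Analysis) describes one efficacy model: "A multivariate analysis of covariance (MANCOVA) will then be conducted", with "dependent variables: scores obtained in the neuropsychological and psychological measures". The design is justified on the ground that "the dependent variables concerning the executive functions (WCST, alternate fluency, and TMT), as well as visuo-perceptive processing (ROCF-C), are moderately but significantly associated". No separate test of the primary set is described.

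Section 3 (Expected Results) lists as a limitation that the number of measures "also raises the potential for type I errors". No control is attached to that remark.

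**The concern.** Three sections separate primary from secondary outcomes, and the analysis section merges them. This is a stated choice of dependent variables, not a detail left open.

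The null hypothesis of the joint test is that the arms do not differ on any of the scores. Rejecting it says that some combination of scores differs, in either direction. The primary hypothesis is directional and confined to cognitive flexibility, so the planned test does not answer it. A change in EDE-Q alone, or a worsening, could produce a significant result. The stated rationale, association among four neuropsychological tests, gives no reason to include EDE-Q, WHOQOL-BREF or URICA.

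At stake is the main claim of the trial: a significant MANCOVA could be reported as support for the primary hypothesis when no flexibility measure had moved. To reach the hypothesis as worded, someone must look at individual instruments, and the article does not say how or with what error control.

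**Working it through.** **Inputs from the article.** Three centers (section 2) with 54 participants each, 27 per group (2.3), give 3 × 54 = 162. Alpha is 0.05, power 0.95, Pillai V 0.2, effect size 0.5 (2.3). Primary instruments: WCST, alternate fluency, TMT, ROCF-C, TAP, DFlex, CFI, so 7. Secondary: EDE-Q, WHOQOL-BREF, URICA, so 3. Total 10.

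**Assumptions.** One change score per instrument, uncorrelated scores unless stated, no covariates, centers pooled. The effects d are standardized differences in change between arms. They are not in the article, so a range is shown.

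**Step 1: the article's own figure.** f² = V/(1 − V) = 0.2/0.8 = 0.25, so f = 0.5, as stated. For one dependent variable at two time points, the group-by-time test has df1 = 1, df2 = N − 2 and noncentrality λ = N × f². At N = 54, λ = 13.5 and power is 0.9501; at N = 53 it is 0.9464. The minimum of 54 reproduces exactly, but for one dependent variable. With the same V and p = 10 joint variables (df1 = 10, df2 = 54 − 10 − 1 = 43), power at N = 54 is 0.60; at N = 162 it is 0.997. The test that was sized is not the test in section 2.7, although at the pooled N the joint test is well powered for V = 0.2.

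**Step 2: rejection with no primary effect.** Let only EDE-Q change. For a two-group test of p variables, df1 = p, df2 = N − p − 1 and λ = N × d²/4. With N = 162 and p = 10, the df are 10 and 151.

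| d on EDE-Q only | λ = 162 × d²/4 | P(joint test significant) |
|---|---|---|
| 0.3 | 3.645 | 0.19 |
| 0.5 | 10.125 | 0.52 |
| 0.7 | 19.845 | 0.86 |

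Correlation among the scores raises these rates. At a common correlation of 0.5, λ is multiplied by (1 + 8 × 0.5)/[(1 − 0.5)(1 + 9 × 0.5)] = 5/2.75 = 1.82, and the d = 0.5 entry becomes 0.83.

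**Step 3: per-instrument testing.** If the 7 primary instruments were each tested at 0.05 without adjustment, family-wise error would be 1 − 0.95⁷ = 0.302 under independence. By simulation with equal correlation it is about 0.27 at 0.3 and 0.23 at 0.5. A Bonferroni level would be 0.05/7 = 0.0071.

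**The case against.** The strongest reply is that this is a condensed article. Follow-up tests and multiplicity rules commonly sit in an analysis plan that is not shown, and an admitted limitation does not prove that the full plan lacks control. That stands to this extent: the article names no follow-up tests, so one cannot say that they are uncontrolled, only that neither tests nor control are stated. The 23% to 30% describes what unadjusted testing would give, not what the article prescribes. The reply does not reach the main point, because section 2.7 itself fixes the set of dependent variables against the article's own hierarchy.

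The rejection rates in Step 2 also depend on assumed effects. That is fair, and hence the range. At d = 0.3 the rate is modest; the logical gap exists at any size.

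A reader might infer three stronger criticisms, which the document does not support.

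- **Dilution of a real flexibility effect.** At N = 162, one flexibility score with d = 0.5 has power of 88–89% alone and 52% among ten uncorrelated variables. But at correlation 0.5 the joint figure is 83%, and if six flexibility scores change by 0.5, as the hypothesis envisages, it exceeds 99%. A loss of power is not shown.
- **A singular model.** Some listed scores are functions of others; the EDE-Q global score is the mean of its subscales. Singularity follows only if totals and components are all entered, and section 2.7 does not say so.
- **Heavy loss through complete-case deletion.** Section 2.7 promises unspecified methods for missing data and does not commit to complete cases. No missingness rate is given, and testing in two sessions per assessment (2.5) suggests that instruments would tend to be missed together.

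**Conclusion.** The point holds in this form: the only efficacy model described merges outcome families that the article keeps apart everywhere else, and its significance would not establish the primary hypothesis. With ten uncorrelated scores and 162 participants, an effect confined to EDE-Q would give a significant joint test in about 19% to 86% of trials as d goes from 0.3 to 0.7. That range rests on one score per instrument and on assumed effects; the mismatch between test and hypothesis needs neither assumption.

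The second part is narrower: the primary hypothesis is worded by instrument and the type I error risk is conceded, but no test that answers it with error control is stated. The defect is one of interpretation and error control, not of pooled power.

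**What to change.** In section 2.7:

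1. Test the primary flexibility measures in their own model, with no secondary measure among the dependent variables.
2. State whether the ROCF-C Central Coherence Index belongs to the primary set. The Introduction adds it after the flexibility instruments, while section 2.5 lists it among the primary outcomes.
3. Base any per-instrument primary claim on one pre-named score per instrument, with a multiplicity adjustment such as Holm.
4. Analyse EDE-Q, WHOQOL-BREF and URICA separately and label them secondary.

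This changes analysis wording only and should be settled before unblinding. The cost is that the sponsor must choose one score per instrument and accept somewhat stricter per-test thresholds; with seven instruments, the smallest p-value would be compared with 0.05/7 = 0.0071 under Holm.

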### 2.3. Sample Size Calculation

The minimum sample size required for this study has been computed using an *a priori* sample size calculator (G*Power 3.1.9.2 software) for the *F* tests [46,47,48]. Participants will be randomly allocated into two groups: (A) TAU plus CA-CRT condition (experimental group) and (B) TAU-only condition (control group). Moreover, the recruits will be assessed before and after the intervention (i.e., 5 weeks). The Pillai V has been set *a priori* to take a value of 0.2, with an effect size of 0.5. Moreover, the type I error (*α*) rate has been set at 0.05 (two-sided), and the power (1 − *β*) at 0.95, respectively. The results showed that there is a 95% chance of correctly rejecting the null hypothesis of no significant interaction effect, with 54 recruits in total (27 per group) for each center.

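### Partial eta-squared, the only effect size named, has no sign and no units, and is biased upward if it is taken from the joint MANCOVA

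*Protocol article*

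**What the plan says.** Section 2.7 of the protocol article plans a MANCOVA with group and time as factors. Its outcomes are given as "dependent variables: scores obtained in the neuropsychological and psychological measures" and its covariates as "covariates: scores obtained in the psychodiagnostic measures at baseline". The effect measure follows: "Partial eta-squared will be used to determine the effect size of the intervention". The section does not say whether this is the multivariate index or one index per outcome, and it names no signed contrast. It does plan group summaries: "Descriptive analyses will be conducted on the experimental group and control group".

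The primary hypothesis in the Introduction is directional: CA-CRT participants "will show significantly greater improvement from baseline to post-treatment than those in the TAU group". The secondary hypothesis is directional as well.

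Section 2.3 sets Pillai's V "to take a value of 0.2, with an effect size of 0.5", and arrives at 54 participants (27 per group) for each of three centers.

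**The concern.** The trial asks whether CA-CRT improves flexibility, coherence and symptoms more than TAU does, and by how much. Partial eta-squared is never negative, so it cannot tell improvement from deterioration. The outcomes also run in different directions (section 2.5): higher is better on the CFI and the Central Coherence Index, higher is worse on the EDE-Q, and the TMT is scored by completion time. A joint index could therefore be sizeable because some outcomes improved while others worsened.

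A second problem arises if the index is multivariate. It then has a positive expected value even with no effect, and that value rises with each score entered. The reported effect size would depend partly on how many indices and subscales went into the model. Section 3 acknowledges the type I error risk from many measures, but not this bias in the effect size.

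**Working it through.** **Inputs.**
- N = 54 per center (section 2.3) and three centers (section 2), so 3 × 54 = 162 pooled.
- Instruments (Introduction): seven primary (WCST, alternate fluency, TMT, TAP, DFlex, CFI, ROCF-C) and three secondary (EDE-Q, WHOQOL-BREF, URICA), so 10 with one score each.
- Number of scores p: the article does not fix it. I use 4 (the four measures named in the rationale for the MANCOVA in section 2.7), 10 (one per instrument) and 20 (if indices and subscales are entered).
- Covariates q = 3, an assumption: the BAI, BDI-II and OCI-R totals.
- No dropout, also an assumption.

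**1. The plan's own figure.** Take a 2 × 2 group-by-time interaction on one outcome. Then f² = V/(1 − V) = 0.2/0.8 = 0.25, so f = 0.5, which matches section 2.3. With df 1 and N − 2, and noncentrality N·f² = 54 × 0.25 = 13.5, power is 0.950 at N = 54. The stated sample size reproduces, for a single outcome.

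**2. Direction.** For one outcome with n per arm, t = d·√(n/2) and partial eta-squared = t²/(t² + df). With n = 27 and df = 52:
- d = +1 or d = −1: t² = 13.5, giving 13.5/65.5 = 0.206 in both cases.
- d = +0.5 or d = −0.5: t² = 3.375, giving 3.375/55.375 = 0.061 in both cases.

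**3. Magnitude.** A one-outcome, 1-df index converts back through |d| = 2√(η²/(1 − η²)): 0.20 gives |d| = 1.0 and 0.06 gives |d| = 0.51. The absolute size is recoverable in standardized form; the sign and the scale units are not.

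**4. Bias of the multivariate index.** With two groups, and two time points reduced to a change, multivariate partial eta-squared equals Pillai's V. Under no effect V follows Beta(p/2, (N − q − p − 1)/2), with mean p/(N − 1 − q).

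| Scores p | Null mean, N = 162 | Null mean, N = 54 |
|---|---|---|
| 1 (per-outcome index) | 1/158 = 0.006 | 1/50 = 0.020 |
| 4 | 4/158 = 0.025 | 4/50 = 0.080 |
| 10 | 10/158 = 0.063 | 10/50 = 0.200 |
| 20 | 20/158 = 0.127 | 20/50 = 0.400 |

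**5. Bias when there is an effect.** Simulating from the noncentral F with a true value of 0.06, N = 162 and q = 3, the mean estimate is 0.067 for p = 1, 0.120 for p = 10 and 0.180 for p = 20.

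**6. Chance of a large value under no effect.** P(V ≥ 0.20) with 10 scores is 0.0002 at N = 162 and 0.46 at N = 54. With 20 scores at N = 162 it is 0.036.

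**The case against.** Partial eta-squared is a conventional companion to MANCOVA, and contrasts with confidence intervals are often left to an analysis plan, which is not shown here. That stands as far as it goes: the absence of those contrasts is not the finding. The finding concerns the measure that section 2.7 does name as the effect size.

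A reader might infer that the trial could not show whether CA-CRT improved anything. The documents do not support that. Descriptive analyses of both groups are planned and the outcomes are measured before and after treatment, so the direction of change would be visible. A 1-df index also converts to an absolute standardized difference. What the descriptives would not supply is the covariate-adjusted effect with its precision.

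A reader might also infer that the index is inflated whatever is done. That holds only for the multivariate version, and its size depends on p and N; per outcome the bias is negligible.

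The most striking comparison is that 10 scores at N = 54 give a null mean of 0.20, equal to the planning value of V. It should not be pressed. The 54 is a per-center number, section 2.7 describes one analysis and no per-center analyses, and the planning V reproduces for one outcome rather than ten. A V of 0.20 in that setting would also come with a p-value of 0.46 and be read as null. The distortion is in the reported effect size, not in the test.

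**Conclusion.** The concern holds in a limited form. The only effect size that section 2.7 names is unsigned and unit-free, so by itself it cannot express the directional hypotheses or the precision of the effect. This needs no assumptions.

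The upward bias is conditional on the index being taken from the joint MANCOVA, which the article leaves open. With three covariates, no dropout and the pooled 162, the expected null value is about 0.03, 0.06 and 0.13 for 4, 10 and 20 scores. It would be 0.08, 0.20 and 0.40 only if a single center of 54 were analysed. A per-outcome index at N = 162 has a null expectation of about 0.006. The change is worth making because it corrects a stated choice at little cost; the validity of the significance test is not in question here.

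**What to change.** In section 2.7, name as the effect measure, for each outcome, the CA-CRT minus TAU difference at post-treatment adjusted for that outcome's baseline score. Report it in scale units with a 95% confidence interval, together with a standardized difference, and state for each outcome which direction is improvement. Keep partial eta-squared as a supplement and state that it is per outcome.

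The cost is one extra results table and a small amount of analysis work. Adjusting for each outcome's own baseline means a per-outcome model alongside the planned group-by-time MANCOVA, so slightly more than a change of wording. No new data are needed, because these outcomes are already scheduled at baseline and at five weeks.
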